# Impact of web application support versus standard management on adherence with adjuvant hormone therapy in patients treated for breast cancer: the WEBAPPAC study

**DOI:** 10.1186/s12885-023-11242-1

**Published:** 2023-08-09

**Keywords:** Breast cancer, Hormone therapy, Adherence, Quality of life, Cancer survivorship care plan, Telemedicine and mHealth

## Abstract

**Background:**

Non-metastatic breast cancer treatment is mainly based on surgery, with or without chemotherapy, radiotherapy and/or hormone therapy. To reduce the risk of hormone receptor positive (HR+) disease recurrence, hormone therapy is prescribed for at least 5 years. It may induce adverse drug reactions (ADRs) as joint pain, sexual dysfunction, weight increase, fatigue, mood disorders and vasomotor symptoms. Around 30–40% of patients withhold hormone therapy within 5 years after initiation. Based on encouraging results of mobile health in patient follow-up, we developed a web-application addressed for breast cancer patients initiating adjuvant hormonal therapy and aimed to assess its impact on hormone therapy adherence, ADRs management, and health-related quality of life.

**Methods:**

The WEBAPPAC trial is a randomized, open-label, prospective, single-center phase 3 study aiming to assess the interest of a web-application support as compared to standard management among breast cancer patients initiating hormone therapy. The main endpoint is the proportion of patients with hormone therapy adherence failure within 18 months after treatment start, in each arm. Eligible patients will be 1:1 randomized between the WEBAPPAC web-application support (experimental arm,) or standard support (control arm), with stratification on type of hormone therapy (Aromatase inhibitor or Tamoxifen). We plan to enroll 438 patients overall. Failure to hormone therapy will be assessed using the Morisky 8-item self-questionnaire (MMSA8), patient adherence logbook, and medical consultations. Secondary outcomes include hormone therapy adherence at 6 months, pain (Visual Analogue Scale and Brief Pain Inventory), quality of life (EORTC QLQ-C30 and BR23 self-questionnaires), anxiety and depression (Hospital and Depression Scale), and return to work and/or daily activities. The user experience with the WEBAPPAC web-application will be assessed using the System Usability Scale (SUS) questionnaire.

**Discussion:**

Hormone therapy discontinuation or adherence failure in breast cancer patients may be indirectly related to an increased risk of recurrence. A better control of medication adherence, through the detection of side effects and some proposed actions trying to reduce them, appears therefore essential to limit the risk of disease recurrence. The WEBAPPAC web-application thus aims better monitoring and allowing higher level of responsiveness in case of ADRs, thus improving treatment adherence.

**Trial registration:**

NCT04554927, registered September 18, 2020.

**Protocol version:**

Version 2.1 dated from December 21, 2021.

## Background

### Breast cancer, hormone therapy, adverse effects and adherence

With 58,459 new cases yearly in France, breast cancer remains the most common cancer in women [1]. Thanks to breast cancer screening campaigns and improved treatments, the 5-year survival rate is 88% [1]. The treatment of non-metastatic breast cancer is mainly based on surgery, with or without chemotherapy, radiotherapy and/or hormone therapy.

Hormone-dependent breast cancer can relapse long after treatment has ended. Approximately 80% of patients have hormone receptor-positive (HR+) tumors [2]. In France, more than 40,000 new breast cancer patients are yearly treated with adjuvant hormone therapy. Hormone therapy is an anti-cancer treatment with an indirect mechanism of action through the inactivation of estrogen. Tamoxifen, as well as aromatase inhibitors (AI), are used for patients whose tumor tissue immunochemistry identifies positive estrogen receptors and/or positive progesterone receptors (ER+/PR+).

To reduce the risk of recurrence in women with HR + breast cancer, hormone therapy is prescribed for at least 5 years. Tamoxifen has become the gold standard of treatment before menopause while aromatase inhibitors have become established after menopause. Randomized trials and meta-analyses have shown that these hormone therapies lead to a gain in relapse-free and overall survivals [3–5]. Furthermore, as the duration of treatment is fundamental to ensure its effectiveness, hormone therapy is nowadays prescribed between 5 and 10 years depending on the indication [6, 7].

Hormone therapy is responsible for adverse drug reactions (ADRs) that usually occur between one and three months after the start of treatment. These ADRs are related to the absence of estrogen impregnation and vary according to the type of medication used (Tamoxifen® or anti-Aromatase/GnRH analogues) and to the patient’s menopausal status. They are related and intertwined with the menopausal effects in women, whatever the menopause was before diagnosis or occurred during chemotherapy.

The most commonly described ADRs are joint pain [8], sexual dysfunction [9] (with or without gynecological symptoms), weight increase, fatigue, mood disorders (up to anxiety-depression syndrome) and vasomotor symptoms (hot flashes and/or night sweats). ADRs have an impact on patients’ quality of life, but also on adherence to treatment [10, 11]. A study conducted among 8,769 patients treated with adjuvant hormone therapy observed a poor adherence rate of 37% and discontinuation of treatment in 20% of cases within the first year of hormone therapy [12]. Similarly, an observational study in United States showed that more than 30% of patients had discontinued AI two years after starting treatment [13]. The assessment of hormone therapy adherence in this study was based on the use of the Morisky scale© 2006 Donald E. Morisky. A study conducted in Singapore [14] reported that only 41% of 157 women were adherent to hormone therapy in the first 2 years: forgetting to take the treatment and avoiding the hormone therapy side effects were the main reported reasons for non-adherence.

### Cancer survivorship care plan

Adjuvant hormone therapy occurs at the end of a very supervised and reassuring hospital care, which leaves some patients with a feeling of being abandoned [15]. Fatigue induced by treatments is still present, as well as a change in intimate life and fear of recurrence, which leads to many questioning. Such situation can impact the prospects for socio-professional reintegration and the return to daily activities, as well as induce anxiety of depressive syndrome. To reduce the after-effects of the disease and its treatments, with high impact on quality of life, and in line with recommendations, a cancer survivorship care plan (SCP) has been established in our cancer center, with the aim to provide comprehensive and personalized care.

SCP includes, at the medical level, a consultation with the oncologist and the breast nurse about 15 days after the end of radiotherapy, during which hormone therapy is prescribed and potential side effects induced by treatments are discussed. Patients are then seen 6 and 18 months after the start of hormone therapy. In case of medical issue, patients should be referred to their attending physician, who is involved from the beginning of the treatment. Information is systematically shared between general practitioners and specialists in order to optimize the quality of follow-up. Concurrently, a team of breast nurses is available to provide personalized follow-up throughout the treatment process, by listening, assessing the patient’s needs, informing, advising and offering continuous emotional and social support.

### Telemedicine and mHealth

To go further with such personalized follow-up outside the hospital, mobile health offers new perspectives for allowing patients to take a more active role in their care and improving monitoring of ADRs. According to the World Health Organization (WHO), mobile health includes “medical and public health practices that rely on mobile devices such as cell phones, patient monitoring systems, personal digital assistants and other wireless devices” [16]. Telemedicine has shown positive impacts (easier access to information, alerting of caregivers, etc.) in the follow-up of patients treated with anti-vitamin K [17], or the monitoring of type I diabetes [18]. An application monitoring the recurrence of bronchial cancer has shown a better follow-up and an increase in life expectancy of patients [19].

E. Basch et al. conducted a randomized trial among 766 metastatic cancer patients to assess the association between overall survival and electronic monitoring of patient-reported symptoms [20, 21]. Median overall survival was 31.2 months in the experimental group with electronic monitoring, and 26.0 months in the usual care group (p = 0.03), with longer duration of chemotherapy (8.2 months versus 6.3 months in the usual care group, p = 0.002). In 77% of cases, nurses responded to symptomatic alerts. Furthermore, the web-application follow-up reduced the number of emergency room visits and decreased the number of hospitalizations.

### The WEBAPPAC web-application

Based on all these encouraging results of mobile health in patients monitoring, we proposed to implement a dedicated web-application for patients initiating adjuvant hormone therapy for breast cancer and to assess its benefits, notably on medication adherence and quality of life. The WEBAPPAC web-application has been developed as a “companion software”, which allows to provide information and advices to patients through different supports (short video, diagram, text …) and to share with health staff, in her environment, symptoms, ADRs, after-effects and patient’s experience.

The WEBAPPAC web-application (compatible with Smartphone or tablet (Android or Apple system) or computer) allows patients to declare the occurrence of symptoms or side-effects and to immediately obtain an adapted and graduated response by the health staff (Fig. 1). It focuses on specific ADRs usually experienced by breast cancer patients under hormone therapy, such as pain (especially joint pain), sexual disorders (associated or not with gynecological symptoms), weight increase, fatigue, psychological disorders (up to anxiety-depressive syndrome) and vasomotor symptoms (hot flashes and/or night sweats). Importantly, this web-application is installed on personal tools of patients.

**Fig. 1 Fig1:**
[figure not shown]
A graduated immediate response adapted to the patient through the WEBAPPAC web-application

Besides this personalized monitoring, the web-application is intended to improve the management of ADRs induced by hormone therapy, by:

Providing health and dietary advices (physical activities and sports, practical advice, “take care of yourself” advice cards, cooking recipes, etc.)Providing information that will allow patients to apply symptomatic treatments without a prescription in close collaboration with their pharmacist (lubricant, level 1 analgesic, etc.)Referring patients to primary health care professionals (attending physician), organizations and structures adapted to their needs (sports educators, social workers, dieticians, patient associations, etc.).Alerting the nurse accompanying the patient on the breast cancer treatment pathway in the event of non-adherence with the hormone therapy treatment.

However, it is to notice that this device should not be considered as an emergency alert.

In this context, we implemented the WEBAPPAC study, herein presented. To our knowledge, this randomized study is the first one, to date, aiming to evaluate the effectiveness of using a web-application on adherence to adjuvant hormone therapy among breast cancer patients with breast cancer.

### Methods / Design

The WEBAPPAC study is a randomized, open-label, prospective, single-center phase 3 trial aiming to compare the adherence to adjuvant hormone therapy at 18 months between breast cancer patients with the WEBAPPAC web-application support versus standard management. The WEBAPPAC protocol and this manuscript have been written in accordance with standard protocol items, namely recommendations for interventional trials (SPIRIT).

### Primary outcome

The main objective is to evaluate the benefit of the WEBAPPAC web-application on patient adherence to adjuvant hormone therapy for breast cancer 18 months after treatment start.

The primary endpoint of the study is the proportion of patients with adherence failure of hormone therapy within 18 months after treatment start, in each arm. Adherence failure of hormone therapy will be defined by at least one of the following items:

Adherence score less than 6 on the 8-item Morisky questionnaire (MMSA8) [22–25], completed at 18 months;Treatment discontinuation since at least one month, documented in the patient’s adherence notebook;Absence of hormone therapy dispensation for at least one month, documented on the hormone therapy prescription, with traceability of each dispensation noted on the prescription;Permanent discontinuation of hormone therapy as declared by the patient at the 18-month follow-up medical consultation.

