### Secondary outcomes

The secondary objectives are to compare between patients with the web-application support and patients with standard support:

The rate of adherence failure of adjuvant hormone therapy at 6 months, defined similarly as for primary endpoint.The adherence rate to adjuvant hormone therapy at 6 and 18 months, according to the MMSA8 adherence score, assessed 6 and 18 months after initiation of hormone therapy and the proportions of patients with “Low adherence” (score < 6), “medium adherence” (score ≤ 6 and < 8) and “high adherence” (score = 8), at each time. For patients categorized in “Low” or “Medium” adherence, the proportion of patients for whom the breast nurse and/or oncologist were warned.Pain scores according to the Brief Pain Inventory (BPI), at baseline and 18 months after the start of hormone therapy, and according to the numerical scale at each consultation at the center.Quality of life scores at inclusion, 6 months and 18 months, according to the EORTC QLQ-C30 self-questionnaire and the BR23 additional module.Anxiety and depression scores at baseline, 6 and 18 months, according to the HADS scale.Return to work and/or daily activities, through.
the proportion of patients who practice a professional activity 18 months after the hormone therapy start among patients of working age and in activity before the diagnosis of their breast cancer;Return to work and modalities (part-time, adaptation of the workstation…).
Patient satisfaction with their support during the first 18 months of hormone therapy, using a visual analog scale (VAS).Number of calls from patients to the hospital breast nurse over 18 months.Number of appointments proposed with the patient’s oncologist in case of low adherence.Number of appointments with the patient’s oncologist (excluding SCP) related to hormone therapy.

In addition, for patients in the experimental arm only, the appropriation, the ease of use and the degree of satisfaction of patients using the web-application, as well as the actions taken in case of poor adherence or non-adherence to hormone therapy will be evaluated with:

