### Statistical design overview

#### Sample size determination

In literature, discontinuation of adjuvant hormone therapy is reported in 20% of cases. The option of offering patients a web-application rather than an accompaniment by a standard follow-up would appear relevant if it allows to observe a difference in discontinuation rate of at least 10%. According to a two proportion z-test, with a two-sided alpha risk of 5% and a power of 80%, 398 patients (199 per arm) are required to observe a significant difference in the discontinuation rate of at least 10%, assuming an adherence failure rate of 20% in the control arm. To take into account a 10% drop-out rate, we plan to enroll 438 patients overall (219 per arm).

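### The 10-point relevance criterion and 20% control rate are stated for discontinuation, the test is on a broader composite, and discontinuation is not listed as a separate between-arm outcome

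*Protocol article*

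**What the plan says.** **Relevance criterion and size (Sample size determination).** The literature rate is given as "discontinuation of adjuvant hormone therapy is reported in 20% of cases". The app "would appear relevant if it allows to observe a difference in discontinuation rate of at least 10" percent. The calculation is described so: "According to a two proportion z-test, with a two-sided alpha risk of 5% and a power of 80" percent, "398 patients (199 per arm) are required" to detect that difference in the discontinuation rate. The same sentence ends "assuming an adherence failure rate of 20% in the control arm". One figure of 20% thus carries two names.

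**Tested endpoint (Primary outcome; Statistical analyses).** "Adherence failure of hormone therapy will be defined by at least one of the following items":
1. MMAS-8 score below 6 at 18 months;
2. a stop of at least one month recorded in the notebook;
3. no dispensation for at least one month;
4. permanent discontinuation declared at the 18-month consultation.

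The arms are compared by one two-tailed chi-squared test on this composite.

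**Other adherence outcomes (Secondary outcomes).** These are the composite at 6 months ("The rate of adherence failure of adjuvant hormone therapy at 6 months, defined similarly as for primary endpoint") and the MMAS-8 score and its three classes at 6 and 18 months. No line gives items 2 to 4 without the questionnaire. Table 2 shows that dispensation, notebook and patient declaration are collected in both arms at 6 and 18 months.

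**The concern.** The quantity that defines a worthwhile effect is not the quantity tested. A woman who continues her tablets but scores below 6 counts the same as one who has stopped. The article's own Background keeps the two apart: in one cohort of 8,769 patients it reports poor adherence of 37% and, separately, discontinuation of 20% in the first year.

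The trial is open-label and the MMAS-8 is self-reported. The app arm alone also completes the MMAS-8 at 6 weeks and 3 months, receives regular notifications and may get advice on forgetfulness. These features could plausibly move questionnaire answers among continuers without changing how many stop.

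If that happened, the composite and the separately listed MMAS-8 outcome could both favour the app, and no listed comparison would say anything about stopping. Yet the only statement of what counts as relevant is worded as a reduction in discontinuation.

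**Working it through.** **1. The plan's own figure.** Inputs from Sample size determination: 20% v 10%, two-sided 5%, 80% power, 1:1. Pooled-variance z-test, with mean proportion 0.15:

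n = [1.960·√(2·0.15·0.85) + 0.842·√(0.20·0.80 + 0.10·0.90)]² / 0.10² = 198.96, so 199 per arm and 398 in total.

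This matches the article. Enrolment is 398 × 1.10 = 438, also as stated. The arithmetic is sound; the question is which rate the 20% and 10% describe.

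**2. Where discontinuation appears.**

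| Place | Discontinuation alone | Composite | MMAS-8 alone |
|---|---|---|---|
| Relevance criterion | yes | no | no |
| Literature rate of 20% | yes | no | no |
| Control rate in the calculation | no | yes (same 20%, relabelled) | no |
| Primary endpoint and test | no | yes | no |
| Secondary adherence outcomes | no | yes (6 months) | yes (6 and 18 months) |

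**3. Can the composite differ with no effect on stopping?** The documents give no component rates, so this is an illustration. Assume discontinuation of 20% in both arms. Take the composite as 37% in control, borrowing the Background's poor-adherence figure and assuming that it contains the 20%. Take 27% in the app arm.

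- Low MMAS-8 among continuers: (0.37 − 0.20)/0.80 = 21% in control and (0.27 − 0.20)/0.80 = 9% with the app.
- Chance of a significant composite in favour of the app (exact enumeration of two binomials, uncorrected chi-squared): 57% with 199 per arm, 61% with 219.

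The true difference in discontinuation is zero throughout.

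**4. What a separate comparison of items 2 to 4 could show.** Same method, 199 per arm:

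| Assumed rates, control v app | Power |
|---|---|
| 20% v 10% | 81% |
| 30% v 20% | 64% |

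The second row matters because the Background ties its 20% to the first year and also cites more than 30% stopping aromatase inhibitors by two years. At 20% v 10% the 95% confidence interval half-width is 1.96·√(0.16/199 + 0.09/199) = 6.9 points.

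**5. Sensitivity of that comparison to the missing-data rule.** Under Statistical analyses, patients with neither 18- nor 6-month data count as failures in the app arm and as adherent in control. With 219 per arm, true rates 20% v 10%, and an assumed share m per arm with no data, the analysed rates are 0.20(1 − m) v 0.10(1 − m) + m:

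| m | Analysed rates | Power |
|---|---|---|
| 0 | 20.0% v 10.0% | 84% |
| 2% | 19.6% v 11.8% | 62% |
| 5% | 19.0% v 14.5% | 24% |

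If a discontinuation outcome used only this rule, even a small share without data could mask a true 10-point effect.

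**The case against.** The strongest reply is that the stated objective is adherence, not stopping. Fewer women scoring below 6 is a benefit on that objective, and the composite is tested as declared. This stands. The 57% is power for a real effect on the primary endpoint under an assumed split, not a false-positive rate.

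A reader might also infer that discontinuation is not an outcome anywhere in the plan. The document does not support that. Items 2 and 4 are discontinuation, item 3 is close to it, and all three count in the primary and 6-month endpoints. What is missing is a separate between-arm line.

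It can further be said that the sample size section uses the two terms interchangeably, so that on the authors' reading the criterion is tested. That reading is possible, but it equates a literature discontinuation rate with the rate of a wider composite, without support and against the Background's own 37% and 20%.

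Finally, component tables are often left to the full protocol or the analysis plan, and the 18-month MMAS-8 classes would partly reveal a questionnaire-driven result. Both points are fair and limit the weight of the missing table. They do not remove the mismatch between criterion and endpoint, which is in the published text, and MMAS-8 classes alone do not give the proportion who stopped.

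**Conclusion.** The point holds in a limited form. The criterion and the source of the 20% refer to discontinuation; the test refers to a composite that also counts MMAS-8 below 6; discontinuation is only a component, while the questionnaire has its own line. A significant composite would therefore not show, from the listed outcomes, whether fewer patients stopped.

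The 57% rests on three assumptions: discontinuation exactly equal at 20%, a control composite of 37%, and a 10-point composite difference. It shows that the case is possible, not that it is likely.

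Two stronger readings should be avoided. One is that a questionnaire-driven win would be a false positive; it would be a true effect on the declared endpoint. The other is that the trial is already sized for a discontinuation comparison; that is so only if the 18-month rates are near 20% v 10% (81% power, against 64% at 30% v 20%, with 199 per arm) and few patients lack data under the asymmetric rule.

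**What to change.** 1. **Secondary outcomes:** add a between-arm outcome, treatment interruption or discontinuation by month 18, defined as any of items 2 to 4 without the MMAS-8. The name should include interruption, because items 2 and 3 can reflect a one-month gap. Report each of the four items by arm beside the composite. Analyse the new outcome with missing data handled the same way in both arms, alongside the rule in Statistical analyses.
2. **Sample size determination:** reword so that the 10-point criterion and the control rate refer to the composite, and justify the 20% for it or restate it. Keep the composite and its chi-squared test as the only success criterion; reading the criterion on a secondary outcome would create a second, rival definition of success.
3. **Interpretation:** state in advance that a composite difference without a difference in items 2 to 4 will be reported as better questionnaire-scored adherence, not as less discontinuation.

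The cost is one outcome line, one table and a reworded paragraph, with no new data or visits. The downside is one more secondary comparison, with the limited power shown above. If the control rate is restated upward under step 2, the power statement for the primary test has to be restated with it.
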